### Randomization

Individuals eligible for participation can register for the study via a link to an online questionnaire using SoSci Survey [101]. Here, participants must confirm that they meet the inclusion criteria for participating in the study. Then, they will be randomly allocated to one of the study conditions (urban built with high road traffic noise, urban built with low road traffic noise, forest with high road traffic noise, forest with low road traffic noise, and forest with low traffic noise with a mindfulness intervention [the latter is not treated here]). Randomization will be conducted by the random generator within SoSci Survey, showing participants a link to an online scheduling tool [102] with free timeslots for the corresponding condition. Alternatively, participants can book a slot via e-mail or telephone. In this case, randomization is conducted by the study team staff clicking on the random generator within SoSci Survey and proposing the participant-free slots shown by the online scheduling tool in the respective condition.

### Data processing and statistical analysis

We will analyze research questions 1–5 using linear mixed-effects models. We will conduct prespecified models comparing the change from t1 to t2 in the outcome measures between participants in the different conditions. Prior to the analyses, the distributions of all measures will be examined, and data will be checked for influential outliers. The model diagnostics of linear mixed-effects models will be examined to assure that model assumptions are met. Due to the large number of outcome variables and the distinct theoretical background of the outcome variables regarding exposure to nature, the results will be analyzed and published in separate papers. One paper will focus on restoration, stress, attention, and affect. A second paper will focus on rumination.

To include road traffic noise as a predictor in the statistical model, the audio files recorded during every walk will be checked by listening to every recoding and categorizing each one-second time period in which road traffic noise is the dominant sound source. We will then calculate the *L*_Aeq_ (equivalent continuous sound level) for the cumulative time periods in which traffic noise is the dominant sound source as well as the cumulative duration in seconds in which traffic noise is dominant. Next, we will calculate the proportion of time in which road traffic noise is not the dominant sound source in relation to the total time of the recording. Then, we will compute the* L*_AE_ (sound exposure level) for the cumulative time periods in which traffic noise is dominant. Further, we will calculate the L_AE_ for the time periods when traffic noise is not dominant, using 30 dB for times when traffic noise is not dominant. This will result in a *L*_AE_ value including *L*_AE_ when traffic noise is dominant and *L*_AE_ for time periods when traffic noise is not dominant, as well as a corresponding *L*_Aeq_ value including times when traffic noise is dominant and not dominant. Noise will be included in the model as a combined predictor of *L*_AE_ including times when traffic noise is dominant and not dominant and the proportion of time, during which traffic noise is not dominant or by using the *L*_Aeq_ including times when traffic noise is dominant and not dominant. We plan to conduct a first model with vegetation and noise as categorial predictors (forest-urban built; high-low traffic noise) and a second model including noise as a continuous and vegetation as a categorial predictor.

In both models, we will specify fixed effects for conditions (vegetation and noise) and time (before and after the walk). Further, we will include an interaction term between vegetation and noise, as well as a random intercept term accounting for individual differences (one per subject). Additionally, in both models, the group constituting the experimental unit in this study will be entered as a second random intercept (one per group) to account for the hierarchical structure of the data due to the organization of participants into different groups. Since we will be conducting group walks, individuals will be subsamples of the walking groups, and the treatment will be applied to groups, not to individual participants. Therefore, the following model will be used: $$outcome \sim vegetation\times noise (1 |\mathrm{ group}/\mathrm{ subject})$$. If suitable, further exploratory models will be computed. For all analyses, we will set the significance level at .05 and analyses will be conducted with R [100] and R package lme4 [103].

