Nature relatedness will be measured with the 6-item short form of the Nature Relatedness Scale (NR-6; [77]). The construct of nature relatedness [76] is assumed to capture an individual’s interest in nature, fascination with nature, and desired contact with nature. Nisbet and Zelenski [77] understand nature relatedness as encompassing an awareness and understanding of all aspects of the natural world, transcending aesthetically appealing aspects. In the present study, we will apply the German version [78] of the NR-6 (e.g., “I always think about how my actions affect the environment,” “My relationship to nature is an important part of who I am,” and “My ideal vacation spot would be a remote, wilderness area”). The scale encompasses the affective and cognitive elements of the relationship with nature. Participants will be asked to respond to the items on a 5-point Likert scale ranging from 1 (*strongly disagree*) to 5 (*strongly agree*). The NR-6 scale has been shown to have good internal consistency, with a Cronbach’s alpha between .83 and .86 [77].

*Connection to nature*

Connection to nature will be assessed using the Love and Care for Nature Scale (LCS; [79]). The LCS measures the emotional components of the connection between humans and nature with reference to the two terms love and care for nature. The initial version of the LCS was developed by Perkins [79]. Perkins defines the construct of love and care for nature as “deep love and caring for nature which includes a clear recognition of nature’s intrinsic value as well as a personal sense of responsibility to protect it from harm” [79]. The LCS was chosen due to its affective focus on the relationship with nature. In the present study, we will use the 5-item version of the scale. Items (e.g., “I feel a deep love for nature”) are rated on a 7-point Likert scale ranging from 1 (*strongly disagree*) to 7 (*strongly agree*). The scale has been shown to have good internal consistency, with a Cronbach’s alpha of .93 [79].

*Satisfaction with life*

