We will assess age, gender, highest education, main occupation, income, frequency of exposure to nature, previous mindfulness experience, and noise sensitivity. Noise sensitivity will be evaluated with one item, asking participants how strongly they agree with the statement “I am noise sensitive”. The item is rated on a 5-point rating scale ranging from 1 (*do not agree at all*) to 5 (*very much agree*). The approach to assess noise sensitivity with a single question was taken from Brink et al. [86], who introduced this concept. Furthermore, we will ask the participants to describe their emotions through the sounds they heard during the walk. Finally, they will be asked to what extent going for a walk helps them think through personal problems and how their thoughts change when they go for a walk.

Physiological outcome measure

*Skin conductance*

Skin conductance level (SCL) will be measured continuously throughout the experiment with Shimmer3 GSR + sensor wristbands [87]. Electrodes will be placed on the volar phalanges of two fingers of the non-dominant hand. In previous research, SCL was shown to be an effective indicator of physiological stress, and SCL variations reflect changes in arousal [88].

Cognitive test

*Attention*

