### Participants and recruitment

Participants will be recruited by various means. A random sample of 7,000 people will be drawn from the residents’ registration office in the city of Zurich. The sample will be stratified over four age groups, 18–35, 35–50, 50–65, and > 65, to reach people of all ages. These participants will be invited to take part in the study by letter. In addition, students from the universities of Zurich (University of Zurich and Swiss Federal Institute of Technology Zurich) will be recruited via e-mail and by lecturers, who will forward the invitation to their students. The invitation to participate will also be distributed via local newspapers, local web portals, as well as at some of the authors' institution Empa. Furthermore, participants will be recruited through advertising with invitation flyers in public places in Zurich and via a study webpage. Finally, participants will be invited via the snowball sampling method, in which the researchers reach out to their social networks to distribute the invitation in Zurich. Participants will receive a remuneration of 50 CHF. Additionally, two massage vouchers amounting to 120 CHF each will be raffled anonymously among all participants who have completed the t1, t2, and t3 questionnaires. Individuals will be eligible for participation if they: (a) are 18 years and older; (b) are physically able to walk for half an hour at a moderate pace; (c) have no diagnosed hearing problems; (d) do not take cortisone for medical reasons; and (e) have a BMI < 35. The study has been approved by the Ethics Committee of the Swiss Federal Institute of Technology Zurich (Ref No. EK 2021-N-211 of 27.01.2022). The study results will be released to the participants and the public. All data will be identified with an identification number to maintain participant confidentiality. Access to the study data will be restricted to the study team, and all forms related to the study data will be kept in locked cabinets*.*

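### The primary ROS reads as a post-walk rating with no baseline, yet neither prespecified model includes a participant covariate; a short pre-walk set would give a modest gain in precision

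*Protocol article*

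**What the plan says.** The section on data processing and statistical analysis fixes the terms of both models. The fixed effects come first: "In both models, we will specify fixed effects for conditions (vegetation and noise) and time (before and after the walk". Then "we will include an interaction term between vegetation and noise, as well as a random intercept term accounting for individual differences (one per subject"; the walking group "will be entered as a second random intercept (one per group". No participant characteristic is listed. The only opening left is "If suitable, further exploratory models will be computed". The same section says the models serve for "comparing the change from t1 to t2 in the outcome measures between participants in the different conditions".

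Candidate covariates are on the data collection list. Under secondary outcomes: "We will assess age, gender, highest education, main occupation, income, frequency of exposure to nature, previous mindfulness experience, and noise sensitivity", and "Nature relatedness will be measured with the 6-item short form of the Nature Relatedness Scale". On recruitment from the residents' register: "The sample will be stratified over four age groups".

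The primary outcomes section puts the ROS items in the past tense and asks how far the walk contributed to each state. The sample size section, by contrast, uses ROS scores from before and after the walk in an earlier study and powers an environment × time interaction.

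**The concern.** An outcome measured before and after the walk lets each participant act as their own control. An outcome rated only afterwards does not. With one ROS value per person, the subject intercept and the residual are the same quantity. That intercept then absorbs nothing, and stable differences between people (age, attachment to nature, perhaps sensitivity to noise) remain in the error of the forest–urban and high–low noise comparisons. The number of walking groups is small, and the randomization section describes a plain random generator with no balancing on these traits. Adjusting for pre-walk values could tighten the ROS estimates without enrolling anyone. At stake is some precision on a primary outcome, not validity.

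**Working it through.** **The plan's own figure.** The article asks for 19 groups of 1–6 for at least 80% power. Its ROS inputs give a difference in change of (5.16 − 4.60) − (4.20 − 4.56) = 0.92 and a pooled SD of 0.882. The pre–post correlation and the group variance are not given, so 19 cannot be reproduced exactly. With correlation 0 and no between-group variance in change, the SD of change is 0.882 × √2 = 1.247. This needs 29 people per arm, or 58/3.5 = 16.6 groups at a mean size of 3.5 (19.3 at a mean of 3); simulated power at 19 groups is 85%. So 19 is attainable and not shown to be wrong.

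**Case 1: outcome analysed as change.** A stable trait adds the same amount at t1 and t2 and cancels from the difference. The variance ratio (adjusted over unadjusted) for the environment × time contrast is 1.000 at every R², with a standard error of about 0.212 either way at correlation 0.5.

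**Case 2: outcome rated once, after the walk.** With total person variance set to 1, group ICC ρ, group size m and share R² of person-level variance explained, the variance of a group mean is

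- unadjusted: ρ + (1 − ρ)/m
- adjusted: ρ + (1 − ρ)(1 − R²)/m

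ρ (0.05–0.2) and R² (0.10–0.25) are assumptions. For m, 3.5 is the midpoint of 1–6 and 6 is the maximum.

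| ρ | m | R² | unadjusted | adjusted | SE ratio | equivalent extra groups |
|---|---|---|---|---|---|---|
| 0.05 | 3.5 | 0.25 | 0.321 | 0.254 | 0.888 | 26.8% |
| 0.10 | 3.5 | 0.25 | 0.357 | 0.293 | 0.906 | 22.0% |
| 0.10 | 3.5 | 0.10 | 0.357 | 0.331 | 0.963 | 7.8% |
| 0.20 | 6 | 0.10 | 0.333 | 0.320 | 0.980 | 4.2% |

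The first and last rows are the extremes: the standard error falls by 2–11%.

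**Cost in degrees of freedom.** Take 20 × 3.5 = 70 people, four conditions and three covariates. Ignoring clustering, person-level variance is inflated by about 1 + 3/(70 − 4 − 3 − 1) = 1 + 3/62 = 1.048. Break-even is at R² = 1 − 1/1.048 = 0.046, hence little or no net gain below about 5%.

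**Effect on power for the forest–urban ROS difference.** Post-walk scores give 5.16 − 4.20 = 0.96, with SD √((0.97² + 0.82²)/2) = 0.898. With 20 groups of 1–6 and R² from 0.05 to 0.30, the variance ratio runs from 0.97 to 0.76 at ρ = 0.05 and from 0.98 to 0.85 at ρ = 0.2. Power goes from about 98% to 99–99.7%, and from 94% to 94.5–97%, respectively.

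**H3 and H4, for scale only.** If the minimum of 10 groups per environment splits evenly by noise level, each comparison has 5 versus 5 groups. Assume a 0.8 SD effect, ρ = 0.1, m = 3.5, R² = 0.25 and a normal approximation, which is optimistic with so few groups. The standard error is √(2 × 0.357/5) = 0.378 unadjusted and √(2 × 0.293/5) = 0.342 adjusted; power is about 56% and 65%.

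**The case against.** The case against is strong and most of it stands.

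- A reader might infer that the models hold only condition and time. They do not: the vegetation × noise term and both random intercepts are specified.
- A reader might infer that precision is lost on every outcome. The section describes change from t1 to t2, and cortisol, affect and attention fit that description. Case 1 shows that main-effect covariates gain nothing there.
- A reader might infer bias from chance imbalance in age or attachment to nature. Randomisation covers that, and the standard error already reflects it. An unadjusted analysis is valid.
- A reader might treat age as a design factor that must be in the model. It stratifies only the register invitation sample; students, newspaper, flyer and snowball recruits are not stratified, and randomisation is not.
- No passage reports an association of any of these traits with ROS, so their prognostic value is an assumption.
- The article does not say when noise sensitivity is asked, and the same paragraph includes questions about sounds heard during the walk. An answer given after a noisy walk could be affected by condition.

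It can also be said that covariate sets are usually left to an analysis plan. Here, however, the article calls its models prespecified, lists their terms and prints one formula, so the choice is fixed in the text.

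What does not stand is the reply that each participant is their own control on ROS. That needs a t1 rating, and the item wording points against one, although the power calculation and the stated change comparison assume it. The printed formula also has neither time nor a condition × time term. Read literally, it would compare repeated outcomes between persons too, but covariates are not the remedy for that.

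**Conclusion.** The point holds for ROS, if it is rated only after the walk, and for the other outcomes rated once afterwards. For these, a short set of pre-walk covariates would lower the standard error by 2–11% before the small cost in degrees of freedom. This assumes R² of 10–25%, a group ICC of 0.05–0.2 and 3.5–6 people per group; none of these values for R² or ICC comes from the article. For the large forest–urban difference used in planning, power moves by at most about 3 points. The gain could matter more for the within-environment noise contrasts, but that rests on an assumed effect and an inferred number of groups. The point does not extend to outcomes analysed as change, and it does not call the unadjusted result into question. It is a worthwhile, low-cost improvement of modest size.

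**What to change.** 1. State whether ROS is rated at t1, and bring the item wording, the power calculation and the analysis model into line. Everything below depends on this.
2. If ROS is rated only after the walk, analyse it, and the other outcomes rated once after the walk, with a short prespecified covariate set as mean-centred fixed main effects: age and t1 NR-6. Add noise sensitivity only if it is recorded before the walk.
3. With one value per person, keep the group intercept and drop time and the subject intercept for these outcomes.
4. Fix the set before any further outcome analysis, say which waves had already been examined by then, and report the unadjusted result alongside.
5. Add no such main effects to the change analyses in the hope of precision.

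The cost is analysis wording and about two to three person-level degrees of freedom. The variables are already scheduled, so no new data collection is needed. If the covariates explain less than about 5% of the variance, that cost may cancel the gain.

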#### Hypothesis H1

Compared to walking in an urban built environment, taking a walk in a forest leads to a stronger increase in stress reduction (1), restoration (2), positive affect (3), attention (4), nature connectedness (5), and rumination (6) as well as a stronger decrease in negative affect (7).

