### Sample size calculation

A statistical power calculation was conducted for the restoration outcome scale as the primary outcome. A previous study, employing a similar design to the current study, was conducted by Tyrväinen et al. [14], who compared the restorative effects of exposure to a forest, a park, or an urban built environment using the restoration outcome scale. Participants sat in the respective environment for 15 min, followed by a 30-min walk. Based on the mean scores and standard deviations for the restorative outcome scale before and after the walk in the urban built environment and in the forest, reported by Tyrväinen et al. [14] (mean ROS urban built before = 4.56 (SD = 0.89), mean ROS urban built after = 4.2 (SD = 0.97), mean ROS forest before = 4.6 (SD = 0.84), mean ROS forest after = 5.16 (SD = 0.82)), the power for the current study was calculated using a simulation-based approach. For the simulation, a linear mixed effects model was used, taking group effects and participant effects into account by including a random intercept for participant groups as well as for individual participants. The required number of groups was estimated for a desired statistical power of ≥ 80%, calculating the number of simulations with a significant interaction effect of environment × time using R [100]. Power calculation showed that 19 groups with 1–6 participants per group are required to identify statistical differences between the conditions, assuming a power of ≥ 80% and an alpha level of 0.05. Thus, to accomplish an equal number of groups in urban built environments and forests, we are aiming for a minimum of 10 groups in urban built environments and 10 in forests.

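### For outcomes measured before and after the walk, the stated models lack a condition × time term and so target about half of the intended difference in change

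*Protocol article*

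**What the plan says.** H1 is worded as a difference in change between settings: "taking a walk in a forest leads to a stronger increase in stress reduction (1), restoration (2), positive affect (3), attention (4" and so on through the outcome list. H2 to H4 use the same construction for noise, overall and within each setting. The section on data processing and statistical analysis opens in the same spirit: "We will conduct prespecified models comparing the change from t1 to t2 in the outcome measures between participants in the different conditions". The sample size section sized the study by "calculating the number of simulations with a significant interaction effect of environment × time using R [100".

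The model paragraph says that in both planned models (noise categorical, then noise continuous) "we will specify fixed effects for conditions (vegetation and noise) and time (before and after the walk". The one interaction it names is vegetation × noise: "Further, we will include an interaction term between vegetation and noise, as well as a random intercept term". It then closes with "Therefore, the following model will be used", and the formula has vegetation × noise on the fixed side and nested random intercepts for group and subject. Time does not appear in it. Nothing in the paragraph is a condition × time term, a change score or a baseline covariate. Further exploratory models are left open.

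**The concern.** A difference in change between conditions is estimated by a condition × time term, a comparison of change scores, or a comparison of t2 values adjusted for t1. The model paragraph provides none of these. With t1 and t2 values stacked, a model without condition × time fits one common change to all conditions. Its vegetation and noise coefficients are differences in average level, in which pre-walk values, which the walk cannot influence, carry half the weight.

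At stake are the size and precision of the effects reported for every pre/post outcome, including cortisol. The stated power is also at stake, since it was computed for a term that the analysis model does not contain. If the team notices only at analysis, it must either report a diluted contrast or change a published model after data collection.

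**Working it through.** **1. What each place requires**

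| Place in the protocol article | Quantity or term |
|---|---|
| H1–H4 | difference in change between conditions |
| Data processing and statistical analysis, opening | change from t1 to t2, compared between conditions |
| Sample size calculation | environment × time |
| Same analysis section, model text | vegetation, noise, time, vegetation × noise |
| Same analysis section, formula | vegetation × noise only |

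The first three agree with each other. The last two match neither them nor one another.

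**2. Can the outcome be read as a change score?** No. Time, before and after, is listed as a fixed effect, so the outcome is a level. With one change score per person, the subject intercept could not be separated from the residual.

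**3. What the coefficient estimates.** Let d1 and d2 be the between-condition differences at t1 and t2, and D = d2 − d1 the difference in change. With both time points present for each person, the model without condition × time estimates (d1 + d2)/2 = d1 + D/2. Randomisation makes the expected d1 zero, so the target is D/2. In any one sample, the realised d1 stays in the estimate.

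**4. Numbers from the sample size section** (restoration scale: urban 4.56 to 4.20, forest 4.60 to 5.16)
- D = (5.16 − 4.60) − (4.20 − 4.56) = 0.56 + 0.36 = 0.92.
- Equal baselines: 0.92/2 = 0.46.
- Quoted baselines: d1 = 4.60 − 4.56 = 0.04 and d2 = 5.16 − 4.20 = 0.96, so (0.04 + 0.96)/2 = 0.50.

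**5. The plan's own figure.** The 19 groups cannot be reproduced exactly, because the pre/post correlation r and the variance components are not given. A simulation with 19 groups of 1 to 6, random intercepts for group and subject, and two-sided alpha 0.05 gives power for environment × time of about 86–87% at r = 0.1, 93–94% at r = 0.3 and 98–99% at r = 0.5. The stated power of at least 80% is therefore plausible for that term.

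**6. Power for the two contrasts.** Assumptions: 10 against 10 groups, 3.5 people per group (midpoint of 1 to 6), SD 0.88 (mean of the four quoted SDs: (0.89 + 0.97 + 0.84 + 0.82)/4), two-sided alpha 0.05, noncentral t with 16 df.
- Variance of a person's two-time mean: SD²(1 + r)/2.
- Variance of a person's change: 2·SD²(1 − r).
- Standard error: √[(2/10) × variance × (1 + 2.5·ICC)/3.5].

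Example at r = 0.5, ICC = 0.1:
- Level: variance 0.7744 × 0.75 = 0.5808, standard error 0.204, 0.46/0.204 = 2.26, power 56%.
- Change: variance 0.7744, standard error 0.235, 0.92/0.235 = 3.91, power 96%.

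| ICC | r | Level, 0.46 | Level, 0.50 | Change, 0.92 |
|---|---|---|---|---|
| 0 | 0.1 | 79% | 85% | 86% |
| 0 | 0.3 | 72% | 79% | 93% |
| 0 | 0.5 | 66% | 73% | 98% |
| 0 | 0.7 | 61% | 68% | >99% |
| 0.1 | 0.1 | 70% | 77% | 78% |
| 0.1 | 0.3 | 63% | 70% | 87% |
| 0.1 | 0.5 | 56% | 64% | 96% |
| 0.1 | 0.7 | 51% | 58% | >99% |

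The ICC 0.1 rows apply the ICC to the change as well. Under the protocol's random-intercept model a group intercept cancels from the change, and the ICC 0 rows then describe that contrast.

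**7. Direct check of the two models.** Data were simulated from the quoted means (20 groups of 1 to 6, r = 0.5, group share 0.1, 400 runs, covariance treated as known). Without condition × time, the vegetation coefficient averaged 0.52 and was significant in 57% of runs. With it, vegetation × time averaged 0.93 and was significant in 98.5%.

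**The case against.** The strongest reply is that this is a reporting slip. The aim is stated as a comparison of change, the simulation used environment × time, and the formula is visibly incomplete: it lacks the time effect just named and an operator before the random part. That may well be so. It does not remove the contradiction, because the prose as well as the formula names only vegetation × noise, and the article says that this model will be used.

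A reader might infer that the model does not test H1–H4 at all, or presupposes that they are false. The documents do not support that. Participants are randomised, so the expected baseline difference is zero, and the level coefficients have expectation zero exactly when the changes do not differ. They give diluted, less efficient tests of the hypotheses.

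A reader might also take the restoration-scale figures as harm shown for that outcome. The scale was put into the past tense and asks what the walk contributed, which reads as a rating after the walk. If it is collected only at t2, vegetation × noise on that score is a valid comparison. The sample size section nevertheless uses before and after means for it, so the article is ambiguous. The figures here serve as illustration. The article gives no cortisol means or SDs from which to compute a figure for that outcome.

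Finally, the power gap depends on inputs the article does not give. In the table it runs from about 1 point (0.50, ICC 0 or 0.1, r = 0.1) to nearly 50 points (0.46, ICC 0.1, r = 0.7).

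**Conclusion.** The point stands for outcomes measured before and after the walk, cortisol and attention among them. As written, the models do not match the hypotheses, the stated aim or the power calculation. They estimate d1 + D/2 where D is wanted. The halving follows from randomisation and two time points alone, without any assumed correlation or ICC.

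The power figures do rest on assumptions (mean group size, ICC, r). Over the range shown, the level contrast has 51–79% power at 0.46 and 58–85% at 0.50, against 78% to over 99% for the change contrast. The claimed power of at least 80% for environment × time therefore cannot be carried over to the model as written.

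Neither of the two models is labelled primary, and the defect is the same in both. No single loss such as 96% to 56% should be quoted as the consequence, since it belongs to one assumed correlation and one ICC.

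**What to change.** Bring the model paragraph into line with the hypotheses, the stated aim and the sample size section, for both the categorical and the continuous noise model.

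- **Outcomes at t1 and t2:** either vegetation × noise × time with random intercepts for group and subject, plus a group-level time effect if it can be estimated; or outcome_t2 ~ outcome_t1 + vegetation × noise + (1 | group). Choose one before analysis.
- **Cortisol:** two samples are taken before the walk, one on arrival and one directly before the start. State which is the baseline.
- **Restoration scale:** say when it is collected. If only after the walk, use outcome_t2 ~ vegetation × noise + (1 | group), without a subject intercept.
- **Contrasts:** H1, vegetation averaged over noise; H2, noise averaged over vegetation; H3 and H4, noise within forest and within urban built; RQ5, vegetation × noise. In the three-way model each of these is taken on the change, that is, as its interaction with time.

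The cost is a rewritten formula, a few lines of text and a documented modification through the route the article already describes. No new data are needed.

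### For outcomes measured before and after the walk, a group random intercept drops out of the condition × time test, and the printed formula does not contain that test

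*Protocol article*

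**What the plan says.** **Target.** Under Data processing and statistical analysis, the models are described as "comparing the change from t1 to t2 in the outcome measures between participants in the different conditions". Under Sample size calculation, power was obtained by "calculating the number of simulations with a significant interaction effect of environment × time". Both make the difference in change the question.

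**Unit.** The analysis section states that "the treatment will be applied to groups, not to individual participants".

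**Analysis model.** The text says "we will specify fixed effects for conditions (vegetation and noise) and time (before and after the walk", adds a vegetation × noise interaction and one random intercept per subject, and then "the group constituting the experimental unit in this study will be entered as a second random intercept (one per group". The printed formula has vegetation × noise with nested group and subject intercepts. It contains neither time nor any interaction with time.

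**Power model.** The simulation used the same random structure, "including a random intercept for participant groups as well as for individual participants", with no group-by-time component mentioned. It reports 19 groups of 1–6 participants, raised to 10 urban and 10 forest groups.

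**The concern.** The walk happens between t1 and t2. Whatever group members share because of it (weather, traffic events, the guide, the site) can only appear in their change. A group intercept describes what members share at both times, so it carries no information about shared change. The plan states that the second intercept accounts for the hierarchical structure. For a condition × time test it does not, and standard errors are too small whenever change clusters by group.

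The protocol's own premises make some clustering plausible. H2 says noise during the walk alters change, and everyone in a group hears the same walk. The Discussion says noise varies strongly by situation. Table 2 shows within-setting SDs of L_Aeq up to 3.55 dB (setting 1) and 6.70 dB (setting 6, from 2 recordings). In the first model, with noise as high or low, this variation has no term.

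A second problem is that formula, text and power section do not agree on which term is tested. This is a stated model, not a detail left to a later document.

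**Working it through.** **1. The cancellation.** Write Y = fixed part + a(group) + b(subject) + e, with e independent at t1 and t2 with variance σ². For each participant

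D = Y(t2) − Y(t1) = time effect + δ·condition + e(t2) − e(t1).

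Both a and b are gone, so Var(δ̂) = 2σ²(1/n₁ + 1/n₀), with n counting participants. This is the t-test on individual change scores.

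Numerical check: the intercept-only mixed model was fitted to four simulated data sets and its SE for condition × time compared with that of the change-score regression. Three agreed to five decimals (for example 0.19128 and 0.19128). The fourth, on a variance boundary, gave 0.2073 against 0.2089.

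**2. Type I error if change clusters.** Let ICC be the share of the variance of change lying between groups. The documents give no value, so 0.05–0.30 is assumed. Group sizes are assumed uniform on 1–6: E[m] = 3.5, E[m²] = 91/6 = 15.17, ratio 4.33.

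DEFF = 1 + (4.33 − 1) × ICC = 1 + 3.33 × ICC; actual level = 2[1 − Φ(1.96/√DEFF)].

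| ICC of change | DEFF | Level, formula | Level, simulated (20 groups of 1–6) |
|---|---|---|---|
| 0 | 1.00 | 5.0% | 4.8% |
| 0.05 | 1.17 | 7.0% | 6.8–7.8% |
| 0.10 | 1.33 | 9.0% | 8.2–9.1% |
| 0.20 | 1.67 | 12.9% | 13.1–13.9% |
| 0.30 | 2.00 | 16.6% | 16.1–17.1% |

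The simulated ranges at ICC 0.05–0.30 span separate runs. With every group at the maximum of six, the levels are about 8%, 11%, 17% and 22% at ICC 0.05, 0.10, 0.20 and 0.30. A random group effect on change, with group-level degrees of freedom, kept the level between 3.0% and 6.3% in the same settings.

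**3. The stated 19 groups.** Inputs are "mean ROS urban built before = 4.56 (SD = 0.89), mean ROS urban built after = 4.2 (SD = 0.97" and "mean ROS forest before = 4.6 (SD = 0.84), mean ROS forest after = 5.16 (SD = 0.82". Changes are 4.2 − 4.56 = −0.36 and 5.16 − 4.6 = +0.56, a difference of 0.92. The before–after correlation ρ is not given, so it is varied. The test is taken as two-sided.

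- ρ = 0: mean variance of change = [(0.89² + 0.97²) + (0.84² + 0.82²)]/2 = (1.733 + 1.378)/2 = 1.556, SD 1.247.
- ρ = 0.5: SD 0.883.

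With 19 × 3.5/2 = 33.25 participants per arm and independent changes:

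- ρ = 0: 0.92/(1.247 × √(2/33.25)) = 3.01, power Φ(3.01 − 1.96) = 0.85.
- ρ = 0.5: 0.92/(0.883 × √(2/33.25)) = 4.25, power 0.99.

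By simulation, 80% needs about 17 groups at ρ = 0, 13–14 at ρ = 0.3 and 9–10 at ρ = 0.5. So 19 satisfies the target under intercepts only. As a minimum it cannot be regenerated without the undisclosed correlation, variance components and group-size distribution.

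Power at 19 groups when the model carries a group-level change effect (REML, t with G − 2 degrees of freedom):

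| ICC of change | 0 | 0.05 | 0.10 | 0.20 | 0.30 |
|---|---|---|---|---|---|
| ρ = 0 | 0.78 | 0.72 | 0.69 | 0.63 | 0.51 |
| ρ = 0.5 | 0.96 | 0.95 | 0.94 | 0.87 | 0.82 |

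**4. What else the formula could mean.** Null simulations with 20 groups of 1–6 and ICC of change from 0 to 0.30:

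- Outcome is a change score with a group intercept: level 3.6–5.6%. Valid, but the time effect and subject intercept are then redundant.
- Long format without condition × time, testing the vegetation main effect: level 4.1–5.3%. This averages t1 and t2, so it does not test change.
- Long format with condition × time and intercepts only: level 5.1–16.9%.

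**The case against.** The strongest reply is that the analysis section never writes a condition × time term. That interaction is named only in the power section. If the outcome in the formula is a change score, the group intercept is the right term. The same holds for post-only outcomes. As worded under Primary outcomes, the restoration scale asks what the walk contributed, which reads as a post-walk rating, so the outcome used for sizing may be untouched. Shared variance may also be modest: route and pace are set, participants walk in silence, and measured traffic noise enters the second model.

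Much of this stands, and it limits the point to outcomes measured at both times. It does not clear the plan. A time fixed effect and a per-subject intercept imply repeated rows per person. Cortisol, a primary outcome, and the attention test are taken before and after the walk (Procedures). Read literally, the formula would not test change at all. Continuous noise removes only part of what a group shares, and standardised walking does not make the rest zero.

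A reader might infer that the error rate and the power figure are both wrong. The documents do not support that. With no between-group variance in change the test is nominal, and at ρ = 0.5 the 19 groups keep at least 80% power up to an ICC of 0.30.

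**Conclusion.** The point holds in conditional form. The article's sections disagree on whether condition × time is tested. If it is, as the sample size section implies, the walking group is not accounted for in the comparison of change for outcomes measured at t1 and t2. The mechanism is algebra and is certain for complete two-time-point data.

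The size is not certain. Type I error of about 7% to 17% rests on an assumed ICC of change of 0.05 to 0.30 and on group sizes uniform on 1–6. The claim of at least 80% power is unsupported, not refuted: across the values tried, power at 19 groups runs from 0.51 to 0.96. Post-only outcomes are not affected by the cancellation. The model should be corrected before analysis, because cortisol is a primary outcome and the repair is small.

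**What to change.** 1. For outcomes measured at t1 and t2, write the model in full: vegetation × noise × time with all lower-order terms, and a group-by-time random effect, for example (1 + time | group) + (1 | subject). Alternatively, analyse t2 with t1 as covariate and (1 | group).
2. For post-only outcomes, including the restoration scale if it is one, analyse the post score with (1 | group). State which outcomes are post-only.
3. Use Satterthwaite or Kenward–Roger degrees of freedom, since the planned minimum is only 20 groups.
4. Re-run the power simulation with the same model over ICC of change (for example 0–0.2) and before–after correlation. Report the variance components and group-size distribution, and restate power for the planned groups.

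The cost is one random-effects term, a corrected formula and a re-run of the simulation in R. The price is wider intervals and possibly a less favourable power figure. A group-by-time effect still treats walks at the same site as independent; with three sites per condition, that is a separate limitation it does not remove.
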